### Interpretation of ADR Causality

In this study, AEs, ADRs, and serious ADRs will be judged according to the *Administrative Measures on Reporting and Monitoring for Adverse Drug Reaction* issued by the Ministry of Health in 2011 [27]. The evaluation of ADRs follows a 3-level decision-making process, comprising initial reporting by clinical practitioners, assessment by the Expert Committee for ADR Monitoring at the surveillance center, and final determination by panel of senior domestic experts. Based on established assessment criteria, the causal relationship between AEs and PDL will be evaluated according to five key parameters: (1) temporal plausibility, (2) consistency with known mechanisms of action or established adverse reaction profiles, (3) positive dechallenge response, (4) positive rechallenge response, and (5) exclusion of alternative explanations. The correlation between AE and PDL will be divided into six grades: positive, probable, possible, possibly unrelated, to be evaluated, and unable to be evaluated. Those judged to be the first three grades will be classified as ADRs, those judged to be “possibly unrelated” will be classified as AEs, and those judged as “to be evaluated” or “unable to be evaluated” should be rejudged in combination with the original monitoring data. We will conduct thorough evaluations to ultimately confirm the incidence of ADRs associated with PDL. This approach helps to minimize potential biases associated with patient self-reporting and variations in medical practices across different centers. The occurrence characteristics and processes of ADRs will be meticulously documented, with particular emphasis on the timing of ADR onset, the implementation time of intervention measures for ADRs, and the termination time of ADRs.

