Monitoring the unintended effects of a drug (pharmacovigilance or drug safety) is crucial due to limited knowledge of rare or late-stage side effects upon market release of new drugs [13,14]. In recent years, numerous related studies have reported the clinical efficacy of PDL; however, there were few independent safety studies on it, most of which were small scale and exhibited significant variations in reported safety outcomes across different studies [15-18], resulting in inadequate understanding of its safety monitoring. In summary, published safety data on adverse effects of PDL therapy were insufficient, thereby impeding the use of standardized recommendations that are necessary for ensuring drug safety.

Although Chinese patent medicine generally exhibits a low incidence of adverse reactions, the evidence pyramid classification derived from effectiveness evaluations primarily considers randomized controlled trials as high-level evidence. However, this classification standard may not fully meet the evidence requirements for postmarketing drug safety evaluation due to limitations such as short intervention courses or small sample sizes, often resulting in an inability to detect ADRs and differences between groups. For the above reasons, this study intends to adopt a large-scale, multicenter, long-term, noninterventional, observational study design to comprehensively analyze and report on the occurrence of adverse events (AEs) [19].

The mechanism of kidney metabolism and excretion of various drugs and toxins is an important cause of drug nephrotoxicity [20], while studies have shown that most of the AEs related to the urinary system were from treatment with PDL [21]. It can be seen that the kidney damage caused by PDL needs further investigation. As hepatic function plays an essential role in drug metabolism [22], clinical studies are necessary to determine the characteristics of PDL-related hepatotoxicity. Additionally, the influencing factors of other PDL-related adverse reactions are still unclear and may be related to the inherent characteristics of the drug itself, improper usage and dosage, improper combination, repeated administration, or use without indications, which need further investigation and study. Furthermore, a comprehensive study regarding the adverse effects associated with PDL use in patients is imperative to optimize the risk-benefit ratio and alleviate strain on limited health care resources.

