### Quality Control of ADRs

Each monitoring subcenter will formulate the first-level, quality-control rules and quality-control list according to the content of the monitoring program. The information system of each monitoring unit will be reviewed to ensure that the clinical study data are authentic and traceable. The implementation of the study will adhere to the research protocol and standard operating procedures in order to ensure the authenticity and reliability of the research data. The data collected are presented in Table 1.

**Table 1 table1:** Basic information form for administering Pudilan Xiaoyan oral liquid^a^.

Basic information	Before taking the medicine	After taking the medicine		
		7 days	14 days	21 days
Age	✓			
Sex	✓			
Smoking history	✓			
Occupation	✓			
Expense category^b^	✓			
Pathways to admission	✓			
Drinking alcohol	✓			
Western medicine diagnosis	✓			
Traditional Chinese medicine diagnosis	✓			
Past medical history	✓			
Personal history of allergies	✓			
Allergic manifestation	✓			
Previous other adverse drug reactions or events	✓			
Main drug combination: Western medicine, antibiotics, antipyretic analgesia, proprietary Chinese medicine, or other drugs		✓	✓	✓
Blood routine before and after treatment, white blood cell count, granulocyte, routine urine examination, liver function, renal function, ECG^c^ (test sheet within 30 days before treatment), C-reaction protein, influenza virus detection, pathogen detection, and other tests	✓	✓	✓	✓
Adverse reaction occurrence (yes or no)		✓	✓	✓

^a^Patients are visited and examined before and after taking the medication.

^b^Expense category refers to the classification of expenses, such as out-of-pocket (self-funded) costs, expenses covered by medical insurance, and other payment types. It helps in understanding how different types of expenses are categorized based on their funding source or payment method.

^c^ECG: electrocardiogram.

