### Outcome Measures

#### Primary Outcome Measure: Incidence of ADRs

The incidence of ADRs is the primary outcome measure, and we will identify factors that contributed to the occurrence of ADRs. The incidence of ADR will be primarily categorized in accordance with the criteria proposed by the Committee of International Organization of Medical Sciences: very common (≥10%), common (1%-10%, including 1%), occasional (0.1%-1%, including 0.1%), rare (0.01%-0.1%, including 0.01%), and very rare (<0.01%) [28], as well as according to the classification of ADR symptoms by the World Health Organization (WHO) [29]. The WHO classification of organs and systems involved in ADRs will also be referenced [30]. The incidence characteristics and regional distribution will be subsequently analyzed, while concurrently investigating the influencing factors (Table 2).

**Table 2 table2:** Centralized monitoring results of Pudilan Xiaoyan oral liquid in the registered hospitals.

Monitoring result	Description
Categorization	The ADR^a^ was categorized based on general, novel, and severe classifications The classification was based on the organs and systems affected by the ADR The symptoms of the ADR were classified
ADR incidence	The specific event features of each ADR included the incidence rates of various categories and whether they are infrequent or exceptionally rare
Pedogenic properties	Occurrence characteristics of ADRs specific to each category
Geographical distribution	The distribution of ADRs is primarily observed in North China, Central China, South China Each region exhibits distinct characteristics of ADRs
Influencing factors	Days of medication, age, drug combination, etc

^a^ADR: adverse drug reaction.

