### Statistical Analysis

Data review and cleaning work will take the paper monitoring form as the original record, delete redundant and repetitive parts, supplement missing data, modify wrong values, and report about abnormal values. The basic characteristics of the patients will be included. Descriptive analyses will be performed for the primary and secondary outcomes. SPSS Statistics 26 software (IBM Corp) will be used for descriptive analysis. Data conforming to a normal distribution will be described by means and SDs, and those conforming to a skewed distribution will be described by median, minimum, maximum, and IQR scores. Categorical data will be described by frequencies and percentages. A cohort, nested, case-control study will be used. If 1 patient has an ADR, then 4 patients without ADRs will be matched as the control group according to gender, age with 5 years, drug batch, and other factors, at a ratio of 1∶4 to compare the symptoms related to adverse reactions. In addition, the risk factors of adverse reactions will be analyzed. First, the differences of ADR incidence among the possible influencing factors will be compared separately to find the factors with large differences. Then, synthetic minority oversampling technique and group least absolute shrinkage and selection operator methods will be used to identify factors influencing the occurrence of ADRs, while propensity scoring methods will be used to control for confounding variables.

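### Drug combination is tested as a cause of ADRs with an outcome label that may itself depend on co-medication, so adjudication can distort the estimate in either direction

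*Protocol article*

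**What the plan says.** All references are to the Protocol article. PDL is the study drug.

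- **Outcome label.** Under Interpretation of ADR Causality, each adverse event (AE) is judged on five parameters, ending with "5) exclusion of alternative explanations". The grades then decide the label: "Those judged to be the first three grades will be classified as ADRs" (positive, probable, possible), while "those judged to be “possibly unrelated” will be classified as AEs". Events that cannot be graded at first are judged again with the original monitoring data.
- **Exposure.** Table 1, under Quality Control of ADRs, records "Main drug combination: Western medicine, antibiotics, antipyretic analgesia, proprietary Chinese medicine, or other drugs" at 7, 14 and 21 days, alongside whether an adverse reaction occurred.
- **Question.** The Introduction lists suspected causes of PDL-related reactions, among them "improper usage and dosage, improper combination, repeated administration". Table 2, under Primary Outcome Measure, gives the influencing factors as "Days of medication, age, drug combination, etc".
- **Analysis.** Under Statistical Analysis, for each patient with an ADR "4 patients without ADRs will be matched as the control group". Factors are then compared one by one, and oversampling and "group least absolute shrinkage and selection operator methods will be used to identify factors influencing the occurrence of ADRs". Propensity scores are to handle confounding.

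The text describes neither adjudication blind to co-medication nor a factor analysis on all AEs regardless of grade.

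**The concern.** Co-medication appears on both sides of the analysis: it is an exposure whose effect is to be estimated, and it is information that can settle whether an event counts as an ADR. Two errors can follow.

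- **Downward.** A reaction to PDL in a patient who also takes an antibiotic may be graded *possibly unrelated* because the antibiotic could explain it. The same reaction in a patient on PDL alone would be kept.
- **Upward.** A reaction to the antibiotic may be graded *possible* and counted as a PDL reaction. A patient on PDL alone cannot produce such an event.

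A harmful combination could then look neutral, or a harmless one could look like an interaction. The study is meant to guide safe clinical use, and combination is one of three named influencing factors. More patients do not help, because the error lies in the label and not in sampling.

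**Working it through.** **The plan's own figure.** The plan gives no figure on this point. Its only derived number, the rule-of-three sample size, reproduces: 3 / (1/1000) = 3000 (exact calculation 2995). The point does not rest on it.

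**Does any planned step break the circle?** Matching uses gender, age and drug batch, with other factors unnamed. Propensity scores balance covariates. Neither changes which events were labelled ADRs. The three-level review is credited with reducing self-report bias and differences between centres. The text gives one set of parameters for judging causality, so a further level of review does not remove the dependence on co-medication.

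**How far could the label move the estimate?** The documents give no ADR rate, co-medication prevalence or grading error, so every input here is an assumption:

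- p: risk of a PDL reaction, equal with and without co-medication (no true effect)
- s: share of PDL reactions in co-medicated patients graded *possibly unrelated*
- q: risk of an event caused by the other drug
- f: share of those events graded *possible* or higher

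Graded-ADR odds ratio (OR) = odds(p(1 − s) + q·f) / odds(p).

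All-AE OR = odds(p + q) / odds(p), leaving aside events of the infection itself.

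With p = 0.5%:

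| Case | s | q | f | Labelled risk, co-medicated | Graded OR | All-AE OR |
|---|---|---|---|---|---|---|
| No grading error | 0 | 0 | – | 0.5% | 1.00 | 1.00 |
| A quarter downgraded | 25% | 0 | – | 0.375% | 0.75 | 1.00 |
| Half downgraded | 50% | 0 | – | 0.25% | 0.50 | 1.00 |
| Half of other drug's events pass | 0 | 0.5% | 50% | 0.75% | 1.50 | 2.01 |
| All of other drug's events pass | 0 | 1% | 100% | 1.5% | 3.03 | 3.03 |
| Both errors | 50% | 1% | 25% | 0.5% | 1.00 | 3.03 |

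Worked line: 0.75% gives odds 0.0075 / 0.9925 = 0.00756; 0.5% gives 0.005 / 0.995 = 0.00503; the ratio is 1.50.

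**If there is a true effect.** Take a true risk ratio of 1.5. Let d0 be the share downgraded on PDL alone and d the additional share downgraded in co-medicated patients. The observed ratio is 1.5 × (1 − d0 − d) / (1 − d0).

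- With d0 = 0: d = 20%, 40%, 60% gives 1.2, 0.9, 0.6, and d = 1/3 gives 1.0.
- With d0 = 20% and d = 40%: 1.5 × 0.4 / 0.8 = 0.75.

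**What the table shows.** The label alone can push the estimate down, push it up, or leave it at 1.00 by cancellation. The all-AE comparison is right when the only error is downgrading. It is no more specific to PDL when the other drug causes events of its own.

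**The case against.** The strongest reply is that the downward mechanism is inferred. The article lists five parameters and six grades but does not say how one leads to the other, and *possible* already counts as an ADR. If a competing drug only moves an event from *probable* to *possible*, then s = 0 and nothing is lost. The parameter also does not name co-medication; the infection is another alternative explanation. This stands. A reader might infer that the plan builds in a falsely protective effect of combination, but the text does not support that. The upward error remains possible even under this reading.

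Second, any causality-graded outcome depends on alternative causes, and the factor analysis is exploratory. This is true, and it limits the weight of the point. It does not answer it for the one factor that is itself an alternative cause.

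Third, the Introduction promises a comprehensive report of AEs, and an article may leave sensitivity analyses to a fuller document. The omission alone would be no finding. The point rests on how the stated label, factor and outcome combine.

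Fourth, a reader might conclude that all AEs should become the main outcome, or that patients with *possibly unrelated* events should be barred from the controls. Neither follows. The first replaces the question about PDL-related reactions: with a 1% risk from each drug, no interaction and half of the other drug's events graded *possible*, the graded risk ratio is (1% + 0.5%) / 1% = 1.5, but the all-AE ratio is (1% + 1%) / 1% = 2.0. The second could remove co-medicated patients from the controls disproportionately and so raise the odds ratio. It would also gain little: if 2% of patients without ADRs had such events (assumption), about 2% of controls would be affected.

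**Conclusion.** The concern holds in a limited form. Co-medication is a factor under study and can also enter the outcome label, adjudication is not described as blind to it, and no planned adjustment removes the dependence. The co-medication estimate may be too low or too high, or right by cancellation. The documents fix neither direction nor size. The graded odds ratios of 0.50 to 3.03 under a true null illustrate what assumed grading errors could do and are not estimates.

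The conclusion assumes that assessors treat another drug as an alternative explanation, which is the natural reading because co-medication is recorded with the reactions. The downward part further assumes that this can move an event below *possible*. The descriptive ADR incidence is not affected: it makes no comparison by co-medication, and causality grading is part of its definition.

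**What to change.** Keep the graded ADR as the outcome of the factor analysis. For drug combination, add to the Statistical Analysis section:

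1. A pre-stated sensitivity analysis on all AEs regardless of causality grade, comparing PDL alone with PDL plus each drug class recorded in Table 1.
2. The same comparison shown by causality grade, so that a deficit or excess can be traced to the *possible* and *possibly unrelated* categories.
3. A rule for interpretation: claim a PDL-specific combination effect only if the graded and all-AE results agree, and otherwise report the finding as dependent on adjudication. Agreement is a minimum condition and not proof, since both ratios can exceed 1 when only the other drug is causing events.

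The cost is a few sentences and one further tabulation. CRF B is already completed for any ADR or AE during the medication period, so no new data collection is needed for that period. The downside is small: the all-AE comparison includes reactions to the other drug and events of the infection, so it describes the combination and not PDL alone.

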### Quality Control of ADRs

Each monitoring subcenter will formulate the first-level, quality-control rules and quality-control list according to the content of the monitoring program. The information system of each monitoring unit will be reviewed to ensure that the clinical study data are authentic and traceable. The implementation of the study will adhere to the research protocol and standard operating procedures in order to ensure the authenticity and reliability of the research data. The data collected are presented in Table 1.

**Table 1 table1:** Basic information form for administering Pudilan Xiaoyan oral liquid^a^.

Basic information	Before taking the medicine	After taking the medicine		
		7 days	14 days	21 days
Age	✓			
Sex	✓			
Smoking history	✓			
Occupation	✓			
Expense category^b^	✓			
Pathways to admission	✓			
Drinking alcohol	✓			
Western medicine diagnosis	✓			
Traditional Chinese medicine diagnosis	✓			
Past medical history	✓			
Personal history of allergies	✓			
Allergic manifestation	✓			
Previous other adverse drug reactions or events	✓			
Main drug combination: Western medicine, antibiotics, antipyretic analgesia, proprietary Chinese medicine, or other drugs		✓	✓	✓
Blood routine before and after treatment, white blood cell count, granulocyte, routine urine examination, liver function, renal function, ECG^c^ (test sheet within 30 days before treatment), C-reaction protein, influenza virus detection, pathogen detection, and other tests	✓	✓	✓	✓
Adverse reaction occurrence (yes or no)		✓	✓	✓

^a^Patients are visited and examined before and after taking the medication.

^b^Expense category refers to the classification of expenses, such as out-of-pocket (self-funded) costs, expenses covered by medical insurance, and other payment types. It helps in understanding how different types of expenses are categorized based on their funding source or payment method.

^c^ECG: electrocardiogram.

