#### Basic Information Form for Administering PDL

The researchers will record the AE information collected during the study period into the safety monitoring case report form (CRF). All patients will be required to complete CRF A (PDL basic information form). If the monitored patient experiences an ADR or AE during the medication period, the monitor will need to fill out CRF B. We will check the monitoring data; enter, encode, standardize, and clean the data; and then conduct a third-party data inspection. Any discrepancies in the data will be addressed by two data administrators who will resolve them after independently verifying the original CRFs.

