## Discussion

### Summary

The practice of traditional Chinese medicine in China spans over 2000 years and has consistently garnered high regard for its precise therapeutic efficacy, minimal adverse effects, and cost-effectiveness [33]. As a proprietary Chinese medicine preparation already on the market, PDL had outstanding efficacy in treating URTI [5]. The action mechanism of PDL has been extensively used in clinical practice. However, it is important to acknowledge that there are no completely safe drugs, and every drug administration carries inherent risks. Therefore, the objective of this study was to closely monitor the safety profile of PDL.

The therapeutic safety of PDL is currently being overlooked during the course of disease treatment. Early identification and a better understanding of its adverse reactions will enhance the drug safety profile of PDL and mitigate the therapeutic costs associated with such reactions.

This study is a continuous registry, hospital-intensive monitoring study. Hospital-intensive monitoring allows the evaluation of efficacy and safety in diverse populations under real-world conditions, including sensitive populations that may not be included in premarketing clinical trials, such as pregnant women, ethnic minority groups, older adult patients, children, patients with multiple comorbidities, and those taking multiple medications. The limitation of centralized monitoring in registry hospitals is that it may underestimate the impact of ADRs, as health care professionals may prioritize serious adverse reactions and overlook general adverse reactions. However, this study will implement a 3-level, quality-control approach, using a professional electronic data management system to mitigate missing and misreported data occurrences and ensure the validity and authenticity of the collected information [19].

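### Table 1 asks only about adverse reactions, and CRF B is triggered only during medication, so adverse events in the 7-day follow-up may miss expert review and lower the recorded ADR incidence

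*Protocol article*

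**What the plan says.** The section Basic Information Form for Administering PDL has CRF A, the basic information form, completed for every patient. Table 1, under Quality Control of ADRs, carries that form's name. Its only event item in the 7-, 14- and 21-day columns is "Adverse reaction occurrence (yes or no". The baseline row on the patient's history, by contrast, covers both earlier reactions and earlier events. The follow-up columns also schedule laboratory work, including "routine urine examination, liver function, renal function, ECG", and concomitant drugs.

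The section on the basic information form is wider: "The researchers will record the AE information collected during the study period into the safety monitoring case report form (CRF". It then sets the trigger for the second form: "If the monitored patient experiences an ADR or AE during the medication period, the monitor will need to fill out CRF B".

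Interpretation of ADR Causality describes three levels, "comprising initial reporting by clinical practitioners, assessment by the Expert Committee for ADR Monitoring at the surveillance center", and then a final panel. What is graded is the adverse event: "The correlation between AE and PDL will be divided into six grades". The three most related grades make an event an ADR, while "those judged to be “possibly unrelated” will be classified as AEs".

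Monitoring Time and Follow-Up gives 3 to 14 days of treatment and 7 further days, in part to observe delayed ADRs.

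**The concern.** By the article's own definitions an ADR is the result of grading an adverse event. A form that asks the site whether a reaction occurred asks for that result at the start. A clinician who attributes a rash or an upset stomach to the infection, or to another drug, can truthfully answer no. The expert committee and the final panel can regrade what is submitted to them, but they cannot recover what is not.

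Three planned results depend on this:

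- **Primary outcome.** ADR incidence is sorted into fixed frequency bands, and events lost before expert review can only lower it.
- **Regional distribution.** If hospitals differ in how readily they call an event a reaction, that difference could look like geography.
- **Nested case-control study.** Controls are drawn from patients without ADRs, so a missed case becomes an eligible control.

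**Working it through.** **1. The provisions side by side**

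| Period | Question shown in Table 1 | CRF B required for | Can an event the site calls unrelated reach levels 2 and 3? |
|---|---|---|---|
| Medication, 3 to 14 days | Adverse reaction only | Reaction or event | Yes, by the CRF B rule, though the scheduled prompt does not ask for it |
| Follow-up, 7 days | Adverse reaction only | Nothing stated | No route is shown |

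During treatment the row is a weaker cue than the CRF B rule needs. In follow-up it is the only event question shown.

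**2. How much observation lies outside the CRF B trigger**

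Share = follow-up days / (treatment days + follow-up days).

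- 3-day course: 7 / (3 + 7) = 70%
- 14-day course: 7 / (14 + 7) = 33%

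These are shares of observed days, not of reactions. The article does not say when reactions tend to start.

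**3. The plan's own figure**

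The sample size section uses the rule of threes at 1/1000: 3 / 0.001 = 3000, as stated. The exact form, ln(0.05) / ln(1 − 0.001) = 2994.2, rounds up to 2995. The figure reproduces. It takes for granted that every event is seen.

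**4. What incomplete capture would do (illustration)**

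Let s be the share of true ADRs that are captured. The article gives no value for s, so every value below is an assumption. The true rate of 1/1000 is also assumed; it is the upper end of the range used for the sample size. With 10,000 patients:

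- expected recorded ADRs = 10,000 × 0.001 × s
- 95% upper bound on the true rate if none is recorded = 3 / (10,000 × s)

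| s (assumed) | Recorded ADRs | Upper bound per 10,000 if none recorded |
|---|---|---|
| 1 | 10 | 3.0 |
| 0.9 | 9 | 3.3 |
| 0.75 | 7.5 | 4.0 |
| 0.5 | 5 | 6.0 |

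Suppose capture is complete during treatment, a fraction f of true ADRs starts in follow-up, and a share c of those is captured. Then s = 1 − f(1 − c), which cannot fall below 1 − f. So s = 0.9, 0.75 and 0.5 need at least 10%, 25% and 50% of reactions to start after treatment. The last row is therefore a pessimistic case unless events are also missed during treatment.

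**The case against.** The strongest reply is that the CRF B rule and the causality section both begin from adverse events. The CRF is said to hold adverse event information for the whole study period, and the possibly-unrelated grade would have little use if only believed reactions were submitted. Table 1 is also an article's list of data items, and the actual forms are not shown. Much of this stands, and it rules out several stronger readings that a reader might infer:

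- **The row is the gate to expert review throughout.** Not supported: during medication any adverse event requires CRF B, whatever its cause.
- **The site judges causality before the three-level process starts.** Not supported: initial reporting by practitioners is level 1. The risk is loss before levels 2 and 3.
- **The row is the only scheduled safety check.** Not supported: blood, urine, liver and renal tests are scheduled at the same visits. They do not close the gap, since the Introduction names gastrointestinal and allergic skin reactions, which such tests would not reliably show.
- **The incidence is biased downward, or will change band.** Not shown. An assumed true 1.2% would drop below the 1% boundary once s is under 1.0 / 1.2 = 0.83, but that start lies just above the boundary. At an assumed 0.05% and s = 0.5 the result is 0.025%, still rare.
- **The article admits this problem.** It concedes underestimation because "health care professionals may prioritize serious adverse reactions and overlook general adverse reactions". That is a different cause, although a reaction-only prompt does nothing to counter it.

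One further limit applies. The section on renal function gives a 7-day time frame for all outcomes without saying when it starts. If it runs from the first dose, follow-up events bear on the primary outcome only for courses shorter than 7 days.

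What remains is that the stated commitment to record adverse event information over the whole study period is backed, after treatment, by neither a form trigger nor an event question.

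**Conclusion.** The concern holds as an internal conflict that leaves a gap in ascertainment. The Table 1 wording does not match the CRF B rule or the unit that is graded for causality. During treatment this is a weak prompt. In the 7-day follow-up, events the site attributes to another cause have no stated route to levels 2 and 3. The primary incidence is at risk of downward bias of unknown size.

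This rests on two assumptions: that Table 1 reflects the wording of the form in use, and that the CRF B trigger stops when treatment stops, as written. If CRF A already asks about any adverse event, and CRF B already runs through follow-up, only the article's text needs correcting.

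**What to change.** - Reword the Table 1 row to *Any adverse event since last contact (yes or no)*.
- Require CRF B for every yes through the end of the 7-day follow-up, whatever the site thinks of the cause.
- Derive ADR status only from the final panel's grade.
- For patients already enrolled, list those answering no who have a newly abnormal scheduled test, or a newly started drug of a kind used to treat a reaction, and query them. This uses data Table 1 already collects, but it will not find every symptom-only event.
- Report incidence separately before and after the form change. Enrolment began in July 2019 and the last case is planned for 30 August 2025, so a late change would otherwise mix two methods of ascertainment in one figure. If enrolment has closed, only the cross-check and a statement of the limitation remain.

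The cost is one line on the form, a data-check program, site queries, more CRF B forms for events that prove unrelated, and possibly a slightly higher reported incidence.
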